## Abstract

**Background:**

Social media is essential in the lives of adolescents, with 97% of US teenagers engaging daily. While it facilitates communication, learning, and identity development, it also poses risks like harmful content exposure and psychological distress, particularly for adolescents in their critical developmental stage. Teaching digital life skills innovatively counters these risks, adapting traditional competencies such as decision-making, problem-solving, creative and critical thinking, communication, interpersonal skills, self-awareness, empathy, and emotional and stress management to digital challenges.

**Objective:**

This study evaluates the accessibility of the “leduin” program, a novel intervention designed to impart digital life skills through Instagram. The program aims to leverage social media’s educational potential, focusing on effective strategies to engage adolescents. Emphasizing accessibility is crucial, as it determines the program’s overall impact.

**Methods:**

The leduin program, developed through intervention mapping, applies behavior change techniques via social media for 9th and 10th graders. It is a 14-week spaced learning curriculum with daily sessions <5 minutes. Emphasizing the “reach” aspect of the reach, effectiveness, adoption, implementation, and maintenance (RE-AIM) model, the recruitment targets diverse educational settings across 6 German states, aiming for inclusivity. Recruitment will involve schools, youth centers, and therapeutic facilities. The study seeks at least 128 participants, a calculated minimum to detect medium-sized effects in the quasi-experimental design and explore varying engagement levels and program responses. Data collection includes preintervention, postintervention, and 6-month follow-up surveys, using multilevel regression, latent growth models, and qualitative analysis to extensively assess reach and gain first insights on effectiveness, acceptance, implementation, and maintenance. The study aims to reveal key factors influencing program participation and interaction; a detailed analysis of engagement patterns will reveal the effectiveness of the recruitment strategies and barriers to participation. Additionally, initial indications of the program’s impact on life skills, social media–related skills, health status, risk behaviors, and academic performance will be analyzed.

**Results:**

Recruitment was planned from May 2023 until the beginning of the leduin program in October 2023. As of March 2024, we have recruited 283 participants.

**Conclusions:**

The leduin program stands as an innovative and essential initiative in adolescent health promotion, harnessing the power of social media to teach important digital life skills. This study highlights the critical role of accessibility in the success of social media interventions. Effective adolescent engagement strategies are imperative, as they dictate the overall impact of such interventions. The insights gained from this study will be instrumental in shaping future programs, laying groundwork for a subsequent, more comprehensive cluster-randomized controlled trial. The study’s design acknowledges the limitations of the current quasi-experimental approach, including the anticipated sample size and the absence of a control group, and aims to provide a foundational understanding for future research in this field.

**Trial Registration:**

Deutsches Register Klinischer Studien DRKS00032308; https://drks.de/search/de/trial/DRKS00032308

**International Registered Report Identifier (IRRID):**

PRR1-10.2196/51085

## Introduction

### Background

Social media, a staple in the lives of 97% of US teenagers [1], facilitates communication, learning, and identity development for adolescents [2-5]. However, the functions and the lack of censorship on these platforms can lead to risks such as addiction, psychological distress, and exposure to harmful content [6-8]. Given the ongoing developmental stage of adolescents [9], they frequently lack the essential social-emotional and cognitive skills required for functional and constructive engagement with social media [10]. These challenges underscore the importance of building social media literacy, a crucial skill that enables adolescents to navigate digital content critically and responsibly [11]. Enhancing media literacy involves teaching adolescents to understand and manage the psychological impacts of digital interactions, including the development of self-regulation and critical thinking skills [12-14].

The widespread use of social media also offers a unique opportunity for preventive health interventions. As a cost-effective platform with a broad reach [3,15-17], social media can play a pivotal role in promoting mental and physical health [18-22]. Its accessibility makes it particularly valuable for reaching socially disadvantaged adolescents, who may engage more frequently with digital platforms, often in dysfunctional ways [23-26]. Thus, social media emerges as a critical tool in enhancing equity in health promotion.

While recognizing the potential of social media in adolescent health promotion, the limited evidence base highlights the need for careful consideration of practical, methodological, and ethical implications [22,27-30]. Current studies focus on engaging content and tailored interventions for diverse needs [20,29,31,32] but often lack a comprehensive, evidence-based approach that integrates psychological mechanisms and behavioral change techniques [30]. This gap extends to the challenge of effectively recruiting adolescents, especially for programs addressing sensitive health issues [33,34]. Recruitment complexities arise from stigma and the need to align with adolescents’ varied interests and obtain parental consent [35-37]. Addressing these challenges necessitates multifaceted strategies: empathetic engagement; using diverse channels; and clearly communicating the benefits while ensuring trust, confidentiality, and cultural sensitivity [38,39]. These methods emphasize the need for a supportive and safe environment, messages that resonate with adolescents, and the involvement of the broader community in the recruitment process for prevention programs.

### Digital Life Skills in the Age of Social Media

Modern prevention strategies must encompass the growing convergence of analog and digital life, acknowledging the diverse challenges in both realms. In this context, promoting life skills emerges as a valuable and effective approach, contributing significantly to overall well-being, academic success, and the reduction of risk behaviors and chronic diseases [40-44].

Life skills, as defined by the World Health Organization [45], include decision-making, problem-solving, creative and critical thinking, communication and interpersonal skills, self-awareness, empathy, and managing emotions and stress. Traditional programs, despite their benefits, face challenges such as high costs and limited accessibility [46,47]. The digital era offers new avenues through e-learning and apps to effectively impart these skills while addressing issues such as substance abuse [48-53] but also necessitates developing digital skills to tackle digital challenges [11,12,54].

### Development of a Digital Life Skills Program (Leduin)

#### Overview

Consequently, we have developed the “leduin” program, using the social media platform Instagram to teach digital life skills in a low-threshold and interactive manner, seamlessly integrated into everyday life. In doing so, we followed the intervention mapping methodology [55], which directs the conceptualization, development, and implementation of health promotion programs. The leduin program is a digital intervention specifically designed to empower adolescents in the 9th and 10th grades with crucial digital life skills to navigate challenges presented by social media and everyday life. The following steps were undertaken to develop the leduin program ([name] and [name], unpublished data, 2024).

#### Logic Model Development

The development of the leduin program began with a comprehensive logic model, addressing the complexities of adolescent life in the context of social media. This model focuses on developing digital life skills that enhance health, reduce risk behaviors, and improve school performance, particularly targeting 9th and 10th graders. This timing is strategic as life skills are especially beneficial and more effectively imparted during such transitional periods in a student’s life [56]. The model was informed by focus groups with 67 adolescents aged 14 to 17 years and heterogeneous educational backgrounds.

#### Psychological Mechanisms Identification

The second step involved identifying psychological mechanisms vital for behavioral change and digital life skills development. The leduin program integrates (1) personal variables such as attitudes and self-efficacy, based on social cognitive theory and the theory of planned behavior [57-59]; (2) environmental factors including social norms and support [60,61]; and (3) information processing mechanisms to optimize message impact [62]. Additionally, it focuses on (4) activating resources to support the development of digital life skills [63].

#### Developing Methodological Framework and Intervention Design

For the third step, we crafted a methodological framework using the behavior change taxonomy [64], tailored to social media context. Influenced by research on social media [65], behavior change techniques in health programs [66], and user preferences [67], we chose Instagram for its interactivity and popularity [3,68]. The program integrates behavior change techniques within Instagram, encompassing (1) content sharing through posts and stories for information dissemination, (2) interactive features such as quizzes for behavioral regulation, (3) material and social incentives to enhance engagement, and (4) social processes such as polling and commenting to encourage participation. These components collectively support habit formation, problem-solving, and identity development related to behavior change (see Table 1 for detailed mechanisms and associated features), with the selection process also being guided by adolescent focus group feedback.

**Table 1 table1:** Mechanisms, exemplary behavior change techniques, and associated exemplary social media features within the social media–based life skills program (leduin).

Mechanism	Exemplary behavior change techniques	Exemplary social media features
Content sharing	Information about (1) health consequences (5.1) Information about (2) social and environmental consequences (5.3) Information about (3) emotional consequences (5.6) Pros and cons (9.2) Salience of consequences (5.2) Instruction on how to perform the behavior (4.1) Verbal persuasion about capability (15.1) Credible source (9.1)	Content sharing methods: posts, tweets, and stories using text, image, and video
Behavioral regulation	Self-monitoring of behavior (2.3) Self-monitoring of outcomes of behavior (2.4) Discrepancy between current behavior and goal (1.6)	Interactive elements like quizzes, sliders (similar to Likert-scale), templates, and question stickers
Incentives	Material incentive (behavior; 10.1) Social reward (10.4)	Raffles and prizes Likes, comments, and direct messages
Social processes	Social comparison (6.2) Social support (unspecified; 3.1) Restructuring the social environment (12.2)	Sliders, polls, and direct messages Direct messages, likes, and group chats Community and account recommendations
Processes initiated	Habit formation (8.3) Problem-solving (1.2) Goal setting (behavior; 1.1) Identity associated with changed behavior (4.1)	Push notifications

#### Program and Module Structuring

In the fourth step of the intervention mapping approach, the leduin program’s structure and modules were developed. It resulted in a 14-week program that encompasses modules on individual, social, and health skills, detailed in Textbox 1. Each module introduces, specifies, applies concepts to risk situations and relates them to everyday life, aligning with World Health Organization life skills education guidelines [69]. Modules cover areas such as emotional and stress management, communication skills, and digital safety. Content is delivered through Instagram stories and feeds using short videos, images, quizzes, and surveys to foster active learning. Additionally, the program incorporates weekly self-care and stress management activities and interactive challenges with prizes to boost engagement. An accompanying analog workbook with journaling activities complements the digital content. This dual approach ensures comprehensive life skills training, emphasizing concise, daily content to promote spaced learning [70], contrasting with traditional massed learning methods.

Contents of the 14 modules of the 14-week social media–based life skills program (leduin) divided into individual, social, and health skills.
**Individual skills (modules 1-4):**
Strengths, goals, emotions, and stress
**Social skills (modules 5-8):**
Communication, needs, boundaries, identity, and peer pressure
**Health skills (modules 9-12):**
Risks, addictions, digital violence, and information
**Cross-module:**
Self-care, stress reduction, problem-solving, and self-reflectionModules 0 and 13 contain introduction and conclusion

### Pilot Study of the Leduin Program

In a pilot study, we assessed the feasibility, acceptance, and engagement of the leduin program, implementing it with 101 students of 9th and 10th-grade in high schools and secondary schools in North Rhine-Westphalia and Lower Saxony, Germany, from November 2022 to February 2023 ([name] and [name], unpublished data, 2024). A total of 13 interviews with participating adolescents aged 14 to 17 years and 6 interviews with their teachers were conducted to evaluate acceptance and initial effectiveness. These qualitative findings indicate that the social media–based prevention program was successfully conducted, well-received by participants, and executed with high commitment. Participants reported positive subjective learning outcomes in social media use, self-care, and stress reduction and perceived the leduin program as personally beneficial and enriching. Although the program yielded favorable results, its accessibility presented a substantial hurdle in the recruitment phase. We conducted informational sessions in schools and a youth center to educate adolescents about the program, enabling them to make informed choices about participating in their leisure time. However, the participation rates varied significantly among schools, with certain classes showing high engagement, while others had minimal involvement. This variation underscores the importance of developing effective strategies to engage adolescents in social media–based prevention programs. Consequently, in the fifth step of the intervention mapping approach as the subject of this study, our focus is to examine and enhance accessibility to guarantee effective program execution.

## Methods

### Overview

The objectives of the accessibility study for the leduin program, grounded in the reach, effectiveness, adoption, implementation, and maintenance (RE-AIM) framework [71], primarily focus on evaluating the first dimension of the framework—“reach”—to identify effective strategies for engaging adolescents in digital life skills interventions on social media. This includes reaching a diverse demographic of 9th and 10th graders, encouraging participation, and ensuring sustained engagement. While also considering the remaining RE-AIM aspects—effectiveness, adoption, implementation, and maintenance—the study mainly seeks to understand the characteristics and engagement levels of participating adolescents and to identify what drives active or low engagement. This understanding is critical for refining recruitment strategies and enhancing the impact of social media–based health interventions for youth.

### Reach

The focal point of our study is to encompass a broad and representative demographic of 9th- and 10th-grade adolescents. To achieve this, we are targeting a diverse population from various school types, including grammar schools, comprehensive schools, secondary schools, and independent schools. Moreover, recognizing the importance of reaching adolescents undergoing high stress, recruitment efforts are also extended to youth centers and therapeutic facilities. We will explore the characteristics of adolescents who have consented to participate. Based on insights from the pilot study, we anticipate varying levels of engagement among the participants: some may actively engage with the program’s social media content, while others may have minimal to no interaction although initially interested. This variance allows for a quasi-experimental design, using engagement levels (ranging from none to high) as the basis for group assignment. Such a design is capable of highlighting differences between these engagement groups, and we will explore the predictors that are associated with active engagement or no or low engagement. We will also conduct a qualitative process evaluation to explore the facilitators and barriers encountered during recruitment. This will involve the recruitment team documenting feedback about the program and information event, as well as the reasons participants choose to join or decline participation. This documentation will be captured both in written form and verbally.

### Effectiveness

The program’s effectiveness will be evaluated by its impact on life skills, social media–related skills, health status, risk behaviors, and school performance. Using the quasi-experimental design, we aim to test the hypothesis that enhancing digital life skills through the intervention leads to improved social media skills and reduced risk behaviors. To detect medium-sized effects, a power analysis indicates the need for 128 adolescent participants (power=0.8, α=.05), aligning with existing evidence of medium effect sizes in digital interventions (d=0.30 to 0.76) [72]. This evaluation will provide crucial data for potential effectiveness, shaping the direction of future trials.

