### Maintenance

A 6-month follow-up will gauge the long-term impact of the intervention on intended outcomes and evaluate interaction and retention rates. These data are crucial for understanding the sustainability of the program’s effects.

The operationalization of these dimensions is summarized in Table 2. The trial will be conducted in a single-group design.

**Table 2 table2:** Overview of the questionnaires used with a single-group design to assess primary and secondary outcomes in preintervention, postintervention, and 6-month follow-up surveys.

Outcome and construct					Questionnaire		Reliability

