### Data Analysis

#### Statistical Methods

Quantitative analyses will vary according to the different dimensions of the RE-AIM framework [71]. The software R Studio (Posit) and SPSS (IBM Corp) will be used [95]. Multilevel logistic regressions will be conducted to evaluate the dimensions of reach, acceptance, and implementation. Here, the extent to which the following variables influence institutions’ initial interest in the program, individuals’ initial willingness to participate in the program, completeness of data, and individual engagement within the program is examined: socioeconomic status, gender, age, mode of recruitment (school, youth center, and therapeutic facility), school type, performance, well-being, life satisfaction, and mental health. The initial interest of institutions in the program is operationalized by the proportion of institutions (schools, youth centers, and therapeutic institutions) that participated in an information session. The initial willingness of individuals to participate in the program is assessed by the percentage of students who decide to participate in the program after an information session. The completeness of data is examined by the percentage of data in the preintervention, postintervention, and follow-up surveys, and individual engagement is measured by the participants’ self-assessment.

For quantitative analyses of the dimensions of reach, effectiveness, and sustainability, mixed-effect multilevel regression analysis with institutions (school, youth center, and therapeutic facility), classes, and individuals as evaluation levels and 3 measurement points (preintervention, postintervention, and follow-up) will be carried out. The multilevel structure will be assumed if the actual design effect resulting from the intraclass correlation is >2 [96]. The influence of covariants such as gender, age, and socioeconomic status will be controlled. In addition, the individual courses in the outcome variables, as described before, will be examined by using latent growth models across the 3 time points. Logistic regressions will be conducted to investigate the impact of the program on participants’ addictive or disordered social media use by comparing pre- and postintervention data.

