### Limitations

The limitations of the described approach include potential sampling bias, as engagement levels and the willingness of schools and youth centers to participate may not represent the broader adolescent population. Schools and youth centers facing significant challenges could be unable to participate in the study due to capacity constraints. This stress could be related to having a particularly burdened student body, affecting representativeness. Moreover, while directly recruiting adolescents for a social media intervention via social media platforms might initially appear to be an effective strategy, it presents substantial challenges in the context of a scientific study. The primary issue lies in the difficulty of reliably verifying adolescents’ identities and securing parental consent in an online environment. Additionally, while data collection itself is not intended to be conducted through social media, motivating adolescents to consistently participate in data collection becomes challenging without a supervised setting. This lack of direct oversight and engagement can significantly impact the reliability and consistency of data collection. Therefore, this approach is considered unfeasible for maintaining the rigorous standards required for scientific research.

The quasi-experimental design, while useful, might not fully account for confounding variables influencing engagement and outcomes. We are launching the leduin program with a digital information event, aiming for cost-effectiveness and wide reach among adolescents from diverse regions. This event serves to arouse interest. However, it is essential to thoroughly explain the scientific study’s framework accompanying the program for informed consent. While this detailed explanation may dampen interest, it is a necessary step to ensure ethical compliance and informed participation. Consequently, we will only be able to examine the characteristics of adolescents who initially agreed to participate in the study and take part in the follow-up survey. This will limit representativeness. Since we are also dependent on the voluntary participation of the participants, dropouts are to be expected, both in the program itself and in the surveys.

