Additionally, relying on social media platforms, Instagram could limit reach to adolescents not actively using or engaging with this platform. The follow-up period of 6 months, although significant, may not be sufficient to fully assess the long-term sustainability of the intervention’s effects. Further, our sample size for evaluating the effectiveness of the intervention is calibrated for detecting medium-sized effects, which, while possible, are not guaranteed.

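### The 80% power stated for 128 participants matches two equal, independent, fully observed groups of 64 and carries no stated allowance for unequal engagement groups, clustering or dropout

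*Protocol article*

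**What the plan says.** The Effectiveness section states that "a power analysis indicates the need for 128 adolescent participants (power=0.8, α=.05"), and supports the choice of a medium effect as "aligning with existing evidence of medium effect sizes in digital interventions (d=0.30 to 0.76"). The Methods paragraph of the abstract calls the number "a calculated minimum to detect medium-sized effects in the quasi-experimental design". The Limitations section says again that "our sample size for evaluating the effectiveness of the intervention is calibrated for detecting medium-sized effects".

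The design is described elsewhere in the article:

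- **Groups.** The Maintenance section says "The trial will be conducted in a single-group design". The comparison is created afterwards, "using engagement levels (ranging from none to high) as the basis for group assignment" (Reach). Statistical Methods says engagement is self-assessed.
- **Clustering.** Recruitment is by school class, youth center and therapeutic facility. The planned analysis is a "mixed-effect multilevel regression analysis with institutions (school, youth center, and therapeutic facility), classes, and individuals as evaluation levels".
- **Loss.** Limitations says "dropouts are to be expected, both in the program itself and in the surveys", and Data Collection reports substantial gaps in the pilot's later surveys.
- **Recruited.** Results reports that 283 had agreed to participate by March 2024.

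The article gives no planning d, sidedness, number of engagement groups, split, intraclass correlation or dropout rate for the calculation.

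**The concern.** A power figure belongs to a particular comparison. The one that yields 128 has two groups of equal size, independent observations and an outcome for everyone. This study cannot set the split, because participants sort themselves by engagement, possibly into more than two levels. It samples young people in classes and institutions, and it expects missing surveys. The article attaches the figure explicitly to the quasi-experimental design, so a reader will take 80% power as a property of that design at 128.

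At stake is how the engagement contrast is read. The Effectiveness section says these results will shape later trials, and the abstract's conclusions foresee a cluster-randomized trial. A reader who believes 128 secures 80% power would give a null contrast more weight than it can bear.

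**Working it through.** **Inputs from the article:** α=.05, power 0.8, N=128, a medium effect, 283 recruited.

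**My assumptions** (the article gives no values): d=0.50 as the conventional medium effect; two-sided test; split 30/70 or 25/75; loss 20% or 30%; design effect (DE) 1.5; pre-post correlation r=0.5 where baseline adjustment is credited.

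**Formula.** For group sizes n1 and n2, the noncentrality is δ = d × √(n1·n2/(n1+n2)). Power is the probability that a noncentral t with n1+n2−2 degrees of freedom exceeds the two-sided .05 critical value. Loss multiplies N by (1 − loss), clustering divides N by DE, and baseline adjustment replaces d by d/√(1−r²), which is 0.50/0.866 = 0.577 at r=0.5.

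**Reproducing 128.**
- 64/64: δ = 0.50 × √32 = 2.83, power 0.801.
- 63/63: δ = 0.50 × √31.5 = 2.81, power 0.795.

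So 128 is the smallest equal-group total that reaches 0.80. Other readings fit less well. A one-sided t-test needs 102, and a single-group pre-post test at a standardized change of 0.5 needs 34. A pre-post test at 0.25 gives 128, but that is not a medium effect. A 12-predictor regression at f²=0.15 gives 127, but the article speaks of d.

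**N=128, d=0.50:**

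| Departure | n1·n2/(n1+n2) | δ | Power, unadjusted | Power, adjusted (r=0.5) |
|---|---|---|---|---|
| None (64/64) | 32.0 | 2.83 | 0.80 | – |
| 30/70 split (38/90) | 26.7 | 2.58 | 0.73 | – |
| 25/75 split (32/96) | 24.0 | 2.45 | 0.68 | 0.80 |
| 20% loss (102.4, equal) | 25.6 | 2.53 | 0.71 | 0.82 |
| DE 1.5 (85.3 effective, equal) | 21.3 | 2.31 | 0.63 | 0.75 |
| 25/75, 30% loss, DE 1.5 (90/1.5 = 60; 15/45) | 11.25 | 1.68 | 0.38 | 0.48 |

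**The 283 recruited, 30% loss** (283 × 0.7 ≈ 198 analysed), **25/75 split:**
- DE 1.5: 198/1.5 = 132, or 33/99; δ = 0.50 × √24.75 = 2.49; power 0.69 unadjusted. Adjusted, δ = 2.87 and power is 0.81.
- DE 1.0: 49.5/148.5; δ = 0.50 × √37.1 = 3.05; power 0.86 unadjusted.
- Detectable d at 80% power, unadjusted: 0.46 at DE 1.0 and 0.57 at DE 1.5.

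**Lower end of the cited range.** At d=0.30 with 64/64, δ = 0.30 × √32 = 1.70 and power is 0.39.

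The design-effect rows assume an analysis that holds α at .05 under clustering. Statistical Methods adopts the multilevel structure only when the design effect exceeds 2. At 1.5 clustering would therefore be left out of the model, and the cost would fall on the stated α rather than on nominal power.

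**The case against.** The article names no test, so the two-group calculation is inferred. An article may leave such detail to a fuller document. That stands as a caution on wording. It does not rescue the figure, because the power claim is stated here and tied to the quasi-experimental design.

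The scenarios are mine and could be milder. Engagement is an individual self-report and can vary within classes, so a full design effect of 1.5 is an upper-end penalty. Against that, the pilot found high engagement in some classes and little in others, so some loss from clustering is likely. Baseline adjustment at r=0.5 offsets a 25/75 split alone (0.80) or 20% loss alone (0.82). It does not offset the combination (0.48), and the article does not credit adjustment in the 128.

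Two stronger readings are tempting, and the article supports neither:

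- **That 80% power is claimed from d=0.30 to 0.76.** The range is cited as evidence for planning on a medium effect. Its midpoint is (0.30+0.76)/2 = 0.53, and Limitations says medium effects are not guaranteed.
- **That the recruited study could easily miss a medium effect.** The article calls 128 a minimum and 283 agreed to take part. Even under the combined assumptions, adjusted power at d=0.50 is about 0.81.

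The article also discloses confounding, expected dropout and the lack of a control group, and it presents effectiveness as a first indication. These points lower the severity. None of them says that power at 128 falls below 0.8 for a medium effect.

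**Conclusion.** The number 128 is arithmetically right for two equal, independent, complete groups at d=0.50. The stated 80% power is not a property of the design described, which has or expects departures on all three counts and states no allowance for any of them. Without adjustment, each single departure tested takes power at 128 to between 0.63 and 0.73; the combined case gives 0.38, or 0.48 adjusted. These sizes rest on an inferred test and on assumed split, loss, design effect and correlation. The direction does not depend on the exact values, because 0.801 leaves no margin.

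The practical effect is softened by the 283 recruited. Reach is the main aim, although life skills and social media–related skills are listed as primary outcomes. This is a point that should be fixed, not one that undermines the study.

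**What to change.** In the Effectiveness section, name the test and the planning effect. State that 128 gives 80% power for d=0.50 only with two equal, independent, fully observed engagement groups. Align the abstract and the Limitations sentence with this.

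Then report power or the detectable effect for the 283 recruited under a stated engagement split, design effect, loss and baseline correlation, using the authors' own values where they have them. With 198 analysed at 25/75, for example, the unadjusted detectable d is 0.46 at design effect 1.0 and 0.57 at 1.5. Power at d=0.50 with design effect 1.5 is 0.69 unadjusted and 0.81 baseline-adjusted.

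The sentence citing d=0.30 to 0.76 can stay. Optionally add that the calculation is for d=0.50 and that power at d=0.30 with 64 per group is 0.39.

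The cost is text only: no further participants and no change in conduct. The stated figure becomes less favourable.
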